## Abstract

**Introduction:**

Post-COVID-19 Syndrome (PCS) includes neurological manifestations, especially fatigue and cognitive deficits. Immune dysregulation, autoimmunity, endothelial dysfunction, viral persistence, and viral reactivation are discussed as potential pathophysiological mechanisms. The post-corona-virus immune treatment (PoCoVIT) trial is a phase 2a randomized, controlled, double-blind trial designed to evaluate the effect of methylprednisolone versus placebo on cognitive impairment in PCS. This trial is designed based on the hypothesised autoimmunological pathogenesis and positive aberrations, employing a series of off-label applications.

**Methods:**

Recruitment criteria include a diagnosis of PCS, a minimum age of 18 years and self-reported cognitive deficits at screening. A total of 418 participants will be randomly assigned to either verum or placebo intervention in the first phase of the trial. The trial will consist of a first trial phase intervention with methylprednisolone versus placebo for six weeks, followed by a six-week treatment interruption period. Subsequently, an open second phase will offer methylprednisolone to all participants for six weeks. Outpatient follow-up visits will take place two weeks after each trial medication cessation. The third and final follow-up, at week 52, will be conducted through a telephone interview. The primary outcome measures an intra-patient change of 15 or more points in the memory satisfaction subscale of the Multifactorial Memory Questionnaire (MMQ) from baseline to follow-up 1 (week 8). Key secondary outcomes include long-term intra-patient changes in memory satisfaction from baseline to follow-up 2 (week 20), changes in other MMQ subscales (follow-up 1 and 2), and changes in neuropsychological and cognitive scores, along with assessments through questionnaires focusing on quality of life, fatigue, and mood over the same periods. Exploratory outcomes involve molecular biomarkers variations in serum and cerebrospinal fluid, as well as structural and functional brain magnetic resonance imaging (MRI) parameters changes related to cognition.

**Perspective:**

This trial aims to contribute novel evidence for treating patients with PCS, with a primary focus on those manifesting cognitive deficits. By doing so, it may enhance comprehension of the underlying pathophysiological mechanisms, thereby facilitating biomarker research to advance our understanding and treatment of patients with PCS.

## Introduction

In late 2019, a new strain of the coronavirus-family, severe acute respiratory syndrome coronavirus 2 (SARS-CoV-2), emerged. It spread rapidly around the world and precipitated the Coronavirus Disease 2019 (COVID-19) pandemic, thereby significantly impacting global public health [13]. Consequently, many patients continue to experience protracted symptoms, commonly referred to as ‘long-COVID’ or post-COVID-19 syndrome (PCS), a condition that poses a substantial burden to society. PCS exhibits an overall estimated prevalence ranged from 7.5 to 41% in non-hospitalized adults and 37.6% in hospitalized adults [18]. The manifestation of PCS is more common among younger and female patients [3, 6]. PCS is defined by the WHO as a persistent condition, lasting at least three months after infection with broad spectrum of symptoms which may affect all organ systems and impairing daily activity [22]. Cardinal neurological symptoms include fatigue and cognitive deficits [5], which impose a significant impact on quality of life [22]. Patients report a range of cognitive deficits such as concentration difficulties, word-finding difficulties, memory lapses, attention problems and “brain fog”. Systematic neuropsychological assessments reveal deficits in processing speed, executive function, phonemic fluency, category fluency, and memory encoding [2].

Pathophysiological mechanisms underlying the development of PCS and persistent neurological manifestations following SARS-CoV-2 infection revolve around ongoing viral persistence and direct viral invasion, reactivation of latent herpesviridae, endothelial/microcirculatory dysfunction, neuroinflammation, and autoimmunological processes [9, 15, 16, 21]. These potential pathomechanisms involve the overactivation of the immune system, characterized by hyperinflammation and cytokine release. A notable contributor is the post-viral induction of autoimmunity, a well-established mechanism observed in other diseases [16, 21], alongside molecular mimicry, where anti-pathogen antibodies cross-react with host proteins [19].

Based on previous findings, we propose that SARS-CoV-2 triggers an immune response resulting in a dysregulated autoimmune system involving both cellular and humoral components. Preliminary studies of our research group have shown an association of neuronal antibodies present in both serum and cerebrospinal fluid (CSF) and pathological montreal cognitive assessment (MoCA) results in patients with cognitive deficits [9, 16, 21]. Reactive autoantibodies in the central nervous system (CNS), detected in both serum and CSF during SARS-CoV-2 infection, have been consistently observed in a significant proportion of patients [7, 10, 12, 17]. While the role of biomarkers as indicators for CNS damage or involvement in pathophysiological processes remains challenging, they represent potential targets for immunosuppressive treatment. The rationale behind an autoimmune genesis hypothesis suggests that methylprednisolone could be a viable treatment approach. This well-established anti-inflammatory glucocorticoid has proven efficacy in treating various diseases suspected to have an autoimmune aetiology, characterized by inflammatory changes or immune overactivity. Examples include multiple sclerosis, chronic inflammatory demyelinating polyradiculoneuropathy, and steroid-responsive autoantibody related encephalitis [14]. While some of these diseases can be cured completely with corticosteroids, others require repeated pulse therapy. There are several controlled trials that employ corticosteroids, particularly methylprednisolone, at similar doses for autoimmune neurological diseases [8, 24]. The use of glucocorticoids has been explored in acute SARS-CoV-2 infections associated with an excessive inflammatory response [1, 11]. Methylprednisolone holds promise in disrupting various immunological triggers, presenting a well-known, generally well-tolerated, cost-effective, and widely available therapeutic option [14]. Our data indicates that off-label administration of methylprednisolone resulted in subjective improvements and enhanced performance on neuropsychological tests in a high proportion of PCS patients with CSF autoantibodies (data in preparation). This underscores the potential efficacy of the chosen treatment approach within this specific patient cohort. To date, no randomized, placebo-controlled trials have examined the effects of methylprednisolone in patients with PCS primarily characterized by cognitive deficits.

## Methods

### Objective of the trial

The post-corona-virus immune treatment (PoCoVIT) trial aims to examine the effect of methylprednisolone versus placebo in patients with cognitive deficits in PCS syndrome in a randomized controlled double-blind trial. Additionally, the trial includes exploratory research to identify potential biomarkers, given the frequent occurrence of CNS reactive autoantibodies in the serum and CSF of patients with PCS, particularly those with neurological symptoms such as cognitive deficits. The PoCoVIT trial may enhance our understanding of treatment strategies, thereby improving patient care. Simultaneously, it contributes to biomarker research advancing our understanding of the disease’s pathomechanisms. The objective is not only to demonstrate improvements in clinically relevant and qualitative patient-oriented measures from baseline to week 8 but also to establish correlations between these measures and objective antibody-related mechanistic indicators derived from baseline CSF, neuroimaging, and biomarkers. The second treatment phase, wherein all patients receive methylprednisolone will provide further insights into whether repetitive corticosteroid pulse therapy proves beneficial in symptom control among patients with PCS.

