AE, Adverse Event; cMRI, cranial magnetic resonance imaging; LPS, Performance testing system (Leistungsprüfungssystem: Subtest 3: Logical Thinking); PROMIS, Patient reported outcomes measurement information system; WAIS-IV, Digit span (forward/backward) from the Wechsler Adult Intelligence Scale-Fourth Edition

^1^Treatment period: Placebo vs Verum begin at day 1 ± 3

^2^Treatment period: Verum begin at day 85 ± 3

^3^Blood sample: autoantibodies, complement system and inflammatory markers

^4^Lumbar puncture: autoantibody testing and inflammatory markers

^5^Blood sample A: Glucose, Na, K, GFR, creatinine

^6^Blood sample B: Differential blood count, glucose, Na, K, HbA1c, GFR, creatinine, TSH, AST, ALT

Patients receive trial information and undergo screening before enrolment. At baseline 1 (B1), participants are scanned using cerebral MRI. At baseline 2 and prior to randomization (B2/R), patients complete a neurological and neuropsychological assessment. Blood and optional CSF samples are collected and assessed potential occurrence of autoantibodies. Selected patients, with or without autoantibodies, may be enrolled, following informed consent, in the biomarker and diagnostic platform receiving additional blood analyses and imaging. The biomarker and diagnostic platforms within our centre serve as databases for the identification of diagnostic and prognostic markers associated with PCS, using both imaging data and blood/CSF samples. After randomization, treatment phase 1 unfolds over six weeks, during which patients are randomly assigned to either verum (methylprednisolone) or placebo treatment. Follow-up 1 occurs two weeks post the cessation of trial medication of treatment phase 1. After a four-week treatment break, the second treatment phase begins with all patients receiving methylprednisolone for an additional six weeks. Follow-up 2 occurs two weeks post the cessation of treatment phase 2. Follow-up 3, scheduled 52 weeks after randomization, comprises a telephone interview and patient-completed questionnaires.

During both treatment phases, each participant undergoes safety and monitoring assessments involving blood tests and ultrasound examination for exclusion of deep vein thrombosis of the lower extremity. Detailed documentation of demographic data, medical history, and clinical assessments is conducted during the trial visits (for details refer to Table 1).

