### Perspective

This trial is based on the hypothesis that an immune system overactivation triggers sustained hyperinflammation and autoantibody production in PCS. Autoantibodies, including those against neurotransmitter receptors, have been identified in several cohorts of patients with PCS [9, 10]. The identification and specification of relative frequencies are still limited due to the broad spectrum of antibodies. Notably, autoantibodies against G protein-coupled receptors (GPCRs), particularly ß2- and a1-adrenoreceptors, angiotensin II-, muscarinic M2-, MAS-, nociception–, and ETA-receptors, have been found in sera from PCS patients with neurological and/or cardiac symptoms [26]. These autoantibodies correlated with symptom severity (e.g., fatigue, vasomotor and cognitive symptoms) in patients with post-acute sequelae of COVID-19 with chronic fatigue syndrome (PACS-CFS) [23]. Our findings indicate that autoantibodies targeting brain epitopes are common in patients with PCS and strongly associated with pathological cognitive screening test, especially when detected in CSF [9, 10]. However, due to the recent nature of this research, the epitopes and nature of these autoantibodies have not yet been fully characterized.

Evidence regarding the effect of immunosuppressive therapeutics is urgently needed. To date there are no proven therapeutic options to treat patients with PCS, which imposes a significant burden on individuals, society, and the economy. Methylprednisolone, chosen as the active treatment in this trial, is a cost-effective pharmaceutical with demonstrated clinical effectiveness in various immune-mediated diseases. Adverse effects are well described, and safety visits are scheduled accordingly in the PoCoVIT trial. An additional major aim of PoCoVIT is to enhance our understanding of the pathophysiological mechanisms underlying the disease paving the way for potential therapeutic approaches. In PCS, the imperative for adequately powered randomized placebo-controlled trials is evident, seeking to replace controversial experimental therapeutic approaches with evidence-based decision making in the future.

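### The mechanistic objective is worded as a marker-response correlation, which cannot separate an antibody-dependent steroid effect from prognosis; the randomised week-8 contrast by antibody status can

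*Protocol article*

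**What the plan says.** The section on the objective of the trial gives two aims to be met together. The first is "improvements in clinically relevant and qualitative patient-oriented measures from baseline to week 8". The second is to "establish correlations between these measures and objective antibody-related mechanistic indicators derived from baseline CSF, neuroimaging, and biomarkers". Neither arm nor a between-arm contrast appears in the second.

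The Introduction takes its steroid-response rationale from off-label use, which gave "subjective improvements and enhanced performance on neuropsychological tests in a high proportion of PCS patients with CSF autoantibodies", and adds: "This underscores the potential efficacy of the chosen treatment approach within this specific patient cohort". The eligibility table has no antibody criterion. Randomisation is stratified by age, sex and MoCA.

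Under the trial description, "Blood and optional CSF samples are collected and assessed potential occurrence of autoantibodies". Footnote 3 of Table 1 places autoantibodies in the diagnostic blood sample, which is scheduled at baseline 2, before treatment.

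The Perspective section reports that "autoantibodies targeting brain epitopes are common in patients with PCS and strongly associated with pathological cognitive screening test".

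The statistical section names a logistic model with treatment and the stratification variables for the primary outcome, and similar models for secondary outcomes. It announces subgroup analyses without naming a subgroup. The biomarker outcome in Table 3 is occurrence and change.

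**The concern.** The question behind the objective is whether methylprednisolone works mainly in patients with autoantibodies. A marker that goes with improvement may do so for two reasons: it modifies the treatment effect (predictive), or it marks patients who would follow a different course on either arm (prognostic). The article itself gives grounds for taking the second seriously, because it ties the antibodies to cognitive status irrespective of treatment.

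Correlating improvement with baseline markers, without regard to arm, mixes the two. A positive correlation could then be reported as support for the autoimmune mechanism when it shows only prognosis. The design already holds what is needed to do better: a concurrent placebo arm up to week 8, and a pre-treatment serum sample. After week 8 all patients are offered methylprednisolone in the open phase, so later data have no concurrent control.

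**Working it through.** **Inputs.** From the statistical section: 15% response on verum, 5% on placebo, 90% power, alpha 0.05, 188 evaluable per group, 10% dropout. Antibody prevalence and CSF uptake are not given as figures. I assume prevalence of 30%, 50% and 70%, and CSF uptake of 100%, 50% and 25%.

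**The plan's own figure.** Pooled two-sided z-test: n = [1.96·√(2·0.10·0.90) + 1.2816·√(0.15·0.85 + 0.05·0.95)]² / 0.10² = 187.05, so 188 per group. Then 188/0.90 = 208.9, so 209 per group and 418 in total. The figure reproduces. (The arcsine method that the article names gives 178; this does not bear on the present point.)

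**Can a correlation separate the explanations?** Take 50% prevalence and keep the arm totals at 15% and 5%.

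| | Verum, Ab+ / Ab− | Placebo, Ab+ / Ab− | Pooled, Ab+ / Ab− |
|---|---|---|---|
| Purely predictive | 25% / 5% | 5% / 5% | 15% / 5% |
| Purely prognostic (risk ratio 3 in both strata) | 22.5% / 7.5% | 7.5% / 2.5% | 15% / 5% |

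- Pooled correlation, both rows: phi = (0.15 − 0.05)·√(0.5·0.5) / √(0.10·0.90) = 0.17.
- The pooled tables also coincide at 30% prevalence (21.7% versus 5%, phi 0.25) and at 70% (12.1% versus 5%, phi 0.11).
- A correlation within verum alone is positive in both rows (25% versus 5%; 22.5% versus 7.5%).
- The treatment contrast by status does differ. Risk ratios are 5 (Ab+) and 1 (Ab−) in the first row, and 3 and 3 in the second. As a ratio of odds ratios, the first row gives 6.33 (6.33/1) and the second 1.13 (3.58/3.16).
- Scale matters. Even in the prognostic row the risk differences are 15 points (22.5 − 7.5) and 5 points (7.5 − 2.5). Unequal risk differences alone are therefore not proof of antibody dependence.

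**How precise would the interaction be?** Wald test on the logit scale: b = logit(verum Ab+) − logit(0.05), because the antibody-negative contrast is zero in both scenarios. The variance is the sum over the four cells of 1/[n·p(1 − p)], and power = Φ(b/SE − 1.96).

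Scenario A: Ab+ respond 15% versus 5%, Ab− 5% versus 5%. At 50% prevalence each cell has 94 patients. Variance = 0.0834 + 3 × 0.2240 = 0.755, so SE = 0.869. With b = 1.210, b/SE = 1.392 and power = Φ(−0.568) = 29%. The expected ratio of odds ratios is 3.35, with a 95% interval of roughly 3.35/5.49 to 3.35 × 5.49, that is 0.61 to 18.4.

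Scenario B: overall verum rate 15% as stated in the plan, with all benefit in Ab+, so verum Ab+ = 0.05 + 0.10/prevalence (38.3%, 25%, 19.3%).

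| Prevalence | 30% | 50% | 70% |
|---|---|---|---|
| A, serum on all | 26% | 29% | 23% |
| B, serum on all | 80% | 58% | 34% |
| B, CSF in half | 51% | 33% | 19% |
| B, CSF in a quarter | 29% | 19% | 12% |

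With a 5% placebo rate, the expected placebo responders in the smaller marker group number 94 × 0.05 = 4.7 at 50% prevalence and 56.4 × 0.05 = 2.8 at 30% or 70%. The Wald figures are therefore approximate.

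**The case against.** The wording is one line in an objectives paragraph, not a model. It does not say that arms would be pooled, and correlating by arm and then comparing the arms would use the placebo group. Subgroup analyses are announced, and a condensed article may leave their definition to the full protocol or SAP. This stands. No one can say from the article that an antibody-by-treatment analysis is absent from the plan, only that the stated objective does not call for one.

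The prognostic link is indirect. It concerns a cognitive screening result, not the later course of memory satisfaction, and MoCA is a stratification factor adjusted for in the primary model. This also stands in part: it weakens the presumption of confounding but does not let an arm-blind correlation identify effect modification.

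The Perspective section concedes that the antibodies are not fully characterised, so a positive/negative split is not self-evident. That is a reason to fix the definition before unblinding.

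Two stronger readings are tempting and are not supported:

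- A reader might infer that the mechanistic aim relies on optional CSF. The objective also lists biomarkers, the outcome section includes serum, and Table 1 schedules serum autoantibodies at baseline 2.
- A reader might infer that enrolling antibody-negative patients costs the primary comparison its power. Figures of 22%, 45% and 68% arise at 30%, 50% and 70% prevalence if the 15% response is assigned to antibody-positive patients only, which lowers the overall verum rate to 8%, 10% and 12%. The plan states 15% for the verum group as a whole, and at that rate 188 per group keeps 90%. Rewording the objective would not alter primary power in any case.

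**Conclusion.** The point holds as a cheap improvement to an exploratory objective. A marker-response correlation that ignores arm gives identical pooled results under prediction and prognosis at each prevalence examined, whereas the randomised contrast by antibody status differs clearly (ratio of odds ratios 6.33 versus 1.13 at 50%). The better analysis is imprecise: about 23% to 29% power in scenario A and 34% to 80% in scenario B with serum data on everyone, and less for CSF. It should be read as an estimate with its interval, not as a test of the hypothesis.

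These sizes rest on assumed prevalences, on a 5% placebo rate in both marker groups, and on complete marker data in 188 per arm. The primary comparison, its power and its error rate are not in question.

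**What to change.** Restate the mechanistic objective as the randomised week-8 contrast by baseline antibody status, labelled exploratory:

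- Fit the primary logistic model plus serum-autoantibody status from the baseline 2 sample and its interaction with treatment.
- Report verum-placebo differences with 95% confidence intervals in antibody-positive and antibody-negative patients, beside the interaction on the odds-ratio scale. Say which scale carries the interpretation.
- Define positivity before unblinding.
- Repeat for CSF status among those with a lumbar puncture, labelled as a selected subset.
- Align this with any antibody subgroup that the SAP already contains. If one exists, only the objective's wording needs to change.

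The cost is wording in the objective and the analysis section. The serum sample and autoantibody testing are already scheduled, and eligibility, visits, sample size and alpha stay as they are. The drawback is a wide interval for the interaction, which should be stated in advance.

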### Trial description and design

The PoCoVIT trial is a prospective, single centre trial (OECD category 2) employing a randomized, double blind, placebo-controlled, 2-arm parallel-group design. Patients with predominantly cognitive deficits are enrolled. Figure 1 provides an overview of the main trial procedures. Methylprednisolone serves as the active treatment (verum), and our hypothesis centres on achieving clinically significant improvement following its administration. The primary endpoint is the intra-patient change in Multifactorial Memory Questionnaire (MMQ) subdomain memory satisfaction by ≥ 15 points from baseline to week 8 [25].

**Fig. 1 Fig1:**
[figure not shown]
Flowchart of the post-corona-virus immune treatment (PoCoVIT) trial

Eleven trial visits, detailed in Table 1, including screening, are planned for each patient. The total trial duration for each participant is one year, including two treatment phases, each consisting of 4 weeks of treatment followed by 2 weeks of tapering.

**Table 1 Tab1:** Visit schedule with assessments

Period/Visit name	Screening	Baseline 1	Baseline 2 &Randomization	Treatment period: Placebo vs Verum^1^			Follow-Up	Treatment period: Verum^2^			Follow-Up	
	S (V1)	B1	B2 (V2)	SV (V3)	SV (V4)	SV (V5)	FU1 (V6)	SV (V7)	SV (V8)	SV (V9)	FU2 (V10)	FU3 (V11)
Trial days	− 28 to 0		− 14 to 0	2	14	28	56	86	98	112	140	365
Time windows	± 3 days											± 30 days
Outpatient visit	•		•	•	•	•	•	•	•	•	•	
Informed consent	•											
Inclusion and exclusion criteria	•											
Randomization			•									
Discharge from trial											•	
*History*												
Demographic data			•									•
Medical history			•									
*Diagnostic assessments*												
Structural cMRI		•										
Diagnostic blood sample^3^			•				•				•	
Lumbar puncture^4^			•									
*Safety assessments*												
Neurological and general physical examination			•				•				•	
Pregnancy test in female patients			•		•		•		•		•	
Blood sample A^5^				•	•	•		•	•	•		
Blood sample B^6^			•				•				•	
Clinical and sonographic exclusion of thrombosis					•				•			
AE questioning			•	•	•	•	•	•	•	•	•	
Concomitant medication			•	•	•	•	•	•	•	•	•	•
*Outcome assessments*												
Patient reported symptoms			•				•				•	•
Multifactorial Memory Questionnaire			•				•				•	•
Short form 36 Health survey			•				•				•	•
Fatigue severity scale			•				•				•	•
Chalder fatigue scale			•				•				•	•
Beck depression inventory-II			•				•				•	
Montreal cognitive assessment			•				•				•	
PROMIS 29			•				•				•	
PROMIS Cognitive Function Short form 4a			•				•				•	
Verbal learning and memory test			•				•				•	
Brief Visuospatial memory test—revised			•				•				•	
WAIS-IV			•				•				•	
Test battery for attention performance			•				•				•	
Trail-making-test A and B			•				•				•	
Regensburger Wortflüssigkeits-test			•				•				•	
Symbol digit modalities test			•				•					
Wortschatztest			•									
LPS			•									
Assessment of self-experienced exposure to IMP						•						
Enrolment in diagnostic and biomarker platform study in a subgroup			•				•					

AE, Adverse Event; cMRI, cranial magnetic resonance imaging; LPS, Performance testing system (Leistungsprüfungssystem: Subtest 3: Logical Thinking); PROMIS, Patient reported outcomes measurement information system; WAIS-IV, Digit span (forward/backward) from the Wechsler Adult Intelligence Scale-Fourth Edition

^1^Treatment period: Placebo vs Verum begin at day 1 ± 3

^2^Treatment period: Verum begin at day 85 ± 3

^3^Blood sample: autoantibodies, complement system and inflammatory markers

^4^Lumbar puncture: autoantibody testing and inflammatory markers

^5^Blood sample A: Glucose, Na, K, GFR, creatinine

^6^Blood sample B: Differential blood count, glucose, Na, K, HbA1c, GFR, creatinine, TSH, AST, ALT

Patients receive trial information and undergo screening before enrolment. At baseline 1 (B1), participants are scanned using cerebral MRI. At baseline 2 and prior to randomization (B2/R), patients complete a neurological and neuropsychological assessment. Blood and optional CSF samples are collected and assessed potential occurrence of autoantibodies. Selected patients, with or without autoantibodies, may be enrolled, following informed consent, in the biomarker and diagnostic platform receiving additional blood analyses and imaging. The biomarker and diagnostic platforms within our centre serve as databases for the identification of diagnostic and prognostic markers associated with PCS, using both imaging data and blood/CSF samples. After randomization, treatment phase 1 unfolds over six weeks, during which patients are randomly assigned to either verum (methylprednisolone) or placebo treatment. Follow-up 1 occurs two weeks post the cessation of trial medication of treatment phase 1. After a four-week treatment break, the second treatment phase begins with all patients receiving methylprednisolone for an additional six weeks. Follow-up 2 occurs two weeks post the cessation of treatment phase 2. Follow-up 3, scheduled 52 weeks after randomization, comprises a telephone interview and patient-completed questionnaires.

During both treatment phases, each participant undergoes safety and monitoring assessments involving blood tests and ultrasound examination for exclusion of deep vein thrombosis of the lower extremity. Detailed documentation of demographic data, medical history, and clinical assessments is conducted during the trial visits (for details refer to Table 1).

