### Eligibility criteria

Patients with PCS and cognitive deficits will be recruited from the specialised outpatient clinic of the Department of Neurology at Charité. Inclusion and exclusion criteria for the trial population are comprehensively outlined in Table 2. Informed consent from all participants is mandatory and will be documented after the screening visit, ensuring at least a 24-h period before baseline 1.

**Table 2 Tab2:** Inclusion and exclusion criteria for trial population

*Inclusion criteria*
1. History of confirmed (PCR or serology) SARS-CoV-2 infection according to WHO criteria
2. Ongoing symptoms of PCS for ≥ 3 months
3. Self-reported predominant cognitive deficits at screening
4. Male or female adult who is 18 years or older at the time of informed consent
5. Subject is willing, understanding, and able to provide informed consent
6. Signed informed consent prior to initiation of any trial related measure
7. For female subject or diverse subjects:
(a) Confirmed post-menopausal state, defined as amenorrhea for at least 12 months, or
(b) If being of childbearing potential:
1. Negative highly sensitive urine or serum pregnancy test before inclusion, and
2. Practicing a highly effective birth control method (failure rate of less than 1%):
(a) combined (oestrogen and progestogen containing) hormonal
(b) contraception associated with inhibition of ovulation (oral/intravaginal/ transdermal), or
(c) progestogen-only hormonal contraception associated with inhibition of ovulation (oral/injectable/implantable), or
(d) Intrauterine device, or
(e) Intrauterine hormone-releasing system, or
(f) Bilateral tubal occlusion, or
(g) Vasectomised partner, or
(h) Heterosexual abstinence
*Exclusion criteria*
1. Any ongoing central nervous system disease
2. Any major psychiatric disease within the last 10 years
3. Previous medical history of gastric ulcer, osteoporosis and/or previous vertebral fractures, rheumatological disease or metabolic disease including diabetes mellitus
4. Ongoing immunosuppressive therapy
5. Patient is pregnant or breastfeeding at screening
6. MMQ memory satisfaction subdomain > 50 points at Screening
7. Current malignant disease (including space-occupying brain tumours)
8. Body weight < 45 kg
9. Severe lactose intolerance
10. Participation in another clinical interventional trial within the last 3 months or five half-lives of the other trial’s IMP, if longer than 6 months previous to informed consent

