### Arms and intervention

Participants will be stratified based on age (> 50 years or ≤ 50 years), sex and cognitive screening assessment results, as determined by the MoCA at baseline 2 (> 26/30 or ≤ 26/30 points). Randomization will occur in a 1:1 ratio, assigning participants to either the verum or placebo group. The total intervention duration per participant is 20 weeks. The initial six weeks constitute a double-blind intervention with a starting dose of body weight-adjusted methylprednisolone or matching placebo. In the verum group, participants receive oral methylprednisolone at a dose of approximately 1 mg/kg body weight, taken once daily for four weeks followed by a two-week tapering phase. Conversely, in the control group participants receive a matching placebo orally once daily for six weeks, adhering to a comparable titration schedule to maintain blinding. Following the initial six-week blinded intervention, a drug-free period of six weeks ensues. This is followed by a second, unblinded treatment phase lasting the same duration with an equivalent tapering scheme. During this phase, all participants receive methylprednisolone Three follow-up visits (week 8, week 20, and week 52) are scheduled in addition to the six safety visits.

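### Table 1 schedules no pregnancy test between day 56 and the open-label methylprednisolone start at day 85, so the last scheduled test is 29 days old at that dose (low severity)

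*Protocol article*

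**What the plan says.** All references are to the protocol article.

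- **Test schedule.** The Table 1 row "Pregnancy test in female patients" has marks at B2 (day −14 to 0), V4 (day 14), FU1 (day 56), V8 (day 98) and FU2 (day 140). There is none at V7 (day 86).
- **Start of each course.** Footnote 1 to Table 1: "Treatment period: Placebo vs Verum begin at day 1 ± 3". Footnote 2: "Treatment period: Verum begin at day 85 ± 3".
- **Break before course 2.** The text below Table 1, after describing follow-up 1, says: "After a four-week treatment break, the second treatment phase begins with all patients receiving methylprednisolone".
- **Who is exposed.** On the second phase, Arms and intervention says: "During this phase, all participants receive methylprednisolone". The same section fixes the allocation: "Randomization will occur in a 1:1 ratio". About half of the participants therefore meet active drug for the first time in course 2.
- **Entry conditions.** For women of childbearing potential, inclusion criterion 7(b) in Table 2 asks for two things. One is "Negative highly sensitive urine or serum pregnancy test before inclusion". The other is highly effective contraception with a failure rate below 1%.

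**The concern.** Course 2 is a fresh start of methylprednisolone after a drug-free period, and everyone receives it. Before course 1 the schedule puts a pregnancy test at the baseline visit, shortly before dosing. Before course 2 it puts one only at follow-up 1, about four weeks earlier. A pregnancy too early to detect on day 56, or conceived afterwards, could be detectable by day 85. Under Table 1 it would not be tested for until day 98. For women first allocated to placebo, this older test precedes their first actual exposure.

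What is at stake is participant safety, namely avoidable exposure of an early pregnancy. The article does not describe the fetal risk of the drug. It does exclude pregnant patients, require contraception and repeat the test during the trial, so the plan itself treats such exposure as something to avoid.

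**Working it through.** **Inputs**

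- Tests: B2 (day −14 to 0), days 14, 56, 98 and 140 (Table 1).
- Course starts: day 1 ± 3 and day 85 ± 3 (Table 1, footnotes 1 and 2).
- Visit window: ± 3 days (Table 1). I apply it to every visit concerned, including B2, to get the widest ranges.
- Total enrolment: 418 (Sample size calculation and statistical analysis).
- Not given in the article: the number of women of childbearing potential, and the time base of the 1% contraceptive failure rate.

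**Step 1. Reproduce the plan's own interval.** Follow-up 1 is on day 56 and course 2 starts on day 85. Days 57 to 84 are 84 − 56 = 28 days, which is the stated four-week break. The days in Table 1 and the text agree.

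**Step 2. Age of the last scheduled test at the first dose** (start day minus test day)

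| | Nominal | Shortest with windows | Longest with windows |
|---|---|---|---|
| Course 1 | 1 − 0 = 1 to 1 − (−14) = 15 days | not needed | 4 − (−17) = 21 days |
| Course 2 | 85 − 56 = 29 days | 82 − 59 = 23 days | 88 − 53 = 35 days |

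The longest gap before course 1 (21 days) is shorter than the shortest gap before course 2 (23 days). The windows do not remove the difference.

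**Step 3. Time on drug before the next test in course 2.** Nominal 98 − 85 = 13 days; shortest 95 − 88 = 7; longest 101 − 82 = 19. In course 1 the corresponding nominal figure is 14 − 1 = 13 days, so the on-treatment test is equally placed in both courses. Only the pre-dose test differs.

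**Step 4. Is the test interval itself unusual?** 56 − 14 = 42, 98 − 56 = 42 and 140 − 98 = 42 days. The tests from day 14 on are evenly spaced.

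**Step 5. Expected number of conceptions that a day-85 test would add to what the day-56 test can find.** If a test turns positive L days after conception, the day-56 test covers conceptions up to day 56 − L and a day-85 test covers them up to day 85 − L. The difference is (85 − L) − (56 − L) = 29 days for any L.

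Expected conceptions = women × annual failure rate × 29/365. Assume 100 to 300 women (100/418 = 24% to 300/418 = 72% of participants) and 1% per year:

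- 100 × 0.01 × 29/365 = 0.08
- 300 × 0.01 × 29/365 = 0.24

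With 1:1 allocation, about half of these (0.04 to 0.12) fall in the former placebo arm. Under these assumptions the figures are upper bounds, because the criterion states a failure rate below 1%. With the longest gap of 35 days, the upper figure becomes 300 × 0.01 × 35/365 = 0.29, still well below one.

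**The case against.** The strongest objection is that Table 1 is not exhaustive. Exclusion criterion 6 needs a memory satisfaction score at screening, yet the table marks that questionnaire first at B2. Exclusion criterion 5 concerns pregnancy at screening, and no test is marked at that visit. The table has no dispensing row either, although drug must reach participants before day 85. The full protocol is not shown and may contain a check at dispensing or conditions for starting phase 2. This stands: the dates are certain, but the absence of any pre-dose check is not.

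A reader might also infer that course 2 falls short of a course-1 standard. The documents do not support that. No section sets a maximum test age before dosing. Inclusion criterion 7 is an eligibility rule, and the 1 to 15 days before course 1 follow from where the baseline visit sits. Nor is the 42-day interval between tests an anomaly, since it is the same from day 14 onward.

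Third, other safeguards exist. Highly effective contraception is mandatory and is the main protection. V7, nominally one day after the first course-2 dose, is an outpatient visit with adverse event questioning and blood sampling, where a suspected pregnancy could be raised. The 13 days of exposure therefore apply only if nothing emerges before day 98. This too stands, and it keeps the expected number small.

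What the objection does not remove is the schedule itself. The article gives pregnancy testing its own row with specific visits, and no other section adds a test before course 2. The entry criteria ask for a negative test as well as contraception, so the plan does not rely on contraception alone when a woman enters the trial.

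**Conclusion.** The point holds as a low-severity, optional safety improvement. As Table 1 is written, the last scheduled pregnancy test is 29 days old (23 to 35) at the first course-2 dose, against 1 to 15 days (21 at most) before course 1. The next test follows about 13 days (7 to 19) into dosing.

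Confidence is high for these dates and lower for the conclusion that no check takes place, because the full protocol is not shown. The size of 0.08 to 0.24 expected conceptions rests on an assumed 100 to 300 women of childbearing potential and an assumed annual time base for the 1% rate. Under those assumptions the expected number of affected pregnancies is well below one.

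A reader might suspect harm to the trial's main result. There is none: the primary outcome is measured at week 8 (day 56), before course 2 begins.

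**What to change.** For women of childbearing potential, add a negative urine pregnancy test immediately before the first course-2 dose and make the start of course 2 conditional on it. Keep the day-98 test. The new test can be done when drug is dispensed, or at home with the result reported to the site. If the full protocol already has such a check, it is enough to show it in Table 1.

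This would bring the test age at the first course-2 dose from 29 days to about 0 to 1 day. For a pregnancy found this way it would avoid about 13 days of exposure before the day-98 test.

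The cost is one extra urine test per woman. Table 1 shows no visit on day 85, so avoiding an additional visit may mean accepting a self-reported home result. Under the assumptions above, course 2 would be withheld for pregnancy from at most about 0.24 women in expectation, so the week-20 and week-52 outcomes are practically unchanged. The sample size and the primary analysis need no change.
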